**Discussion:**

Our aim in using this model is to define a group of individuals at low risk for febrile neutropenia who might be treated with reduced intensity or duration of antibiotic therapy and so reduce the inconvenience and cost of these episodes, as well as to define a group of patients at very high risk of complications who could be subject to more intensive therapies. The project will also help develop methods of IPD predictive modelling for use in future studies of risk prediction.

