## Background

Children undergoing treatment for malignancy have an excellent chance of survival, with overall rates approaching 75% [1]. In most cases, children who die following treatment for cancer do so as a result of their disease, but despite huge improvements in supportive care, around 16% of deaths within 5 years of diagnosis are due to the complications of therapy [2,3]. One such life-threatening complication in immunocompromised children remains infection, which frequently manifests as the occurrence of fever with neutropenia [4].

In adopting a policy of aggressive inpatient intravenous antibiotic use in such episodes, the mortality rate related to these episodes has improved dramatically (from 30% in the 1970s to 1% in the late 1990s) [4]. Intensive care management is required in less than 5% of cases [5-7], although a substantial proportion of children have complications which require specialised care [7]. There remain many episodes of febrile neutropenia (FNP), possibly two-thirds or more, among patients in whom no significant infection is identified and in whom this aggressive management strategy is likely to be excessive [7].

To better inform the clinical management of children with cancer and FNP, there is increasing interest in using risk prediction models (also known as 'prognostic models') and clinical decision rules (CDRs) [8-10]. Risk prediction models utilise multiple prognostic factors in combination to predict the risk of a future health outcome for an individual on the basis of their set of prognostic factor values. A CDR recommends a particular clinical action (or inaction) for an individual on the basis of the prediction (for example, the predicted probability, or 'risk score') derived from the model.

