A robust risk prediction model which identifies those children at very low risk of having a significant infection could result in reduced intensity and/or duration of antibiotic therapy in the hospital. It could also form the basis of a randomised controlled trial (RCT) of alternative management approaches (for example, ambulatory oral antibiotics vs inpatient intravenous antibiotics) and would be the ideal way of informing the sample size required by reliably predicting the proportion of events expected in a low-risk group. This would lead to reduced costs for the healthcare system and the patient and family [11], as well as potentially a better quality of life for all affected. At present, there are many differing policies for the management of FNP in practice [12,13] but a lack of agreement about how and which CDRs, if any, are used.

Assessment of the risk of adverse outcome of each episode of FNP has been undertaken by many different groups, with many of them creating a CDR which aims to allow clinicians to accurately judge risk and treat patients appropriately. However, none of these analyses have resulted in a widely used risk stratification model, and current practice is variable, both in the United Kingdom [12] and internationally [13-15]. Some centres use a risk-stratified, reduced-intensity approach, and others treat all children aggressively. The essential problems with research in this area are common across much of paediatric practice: those of rare conditions with small numbers of cases and limited collaboration in primary studies. The modelling studies that have been done have incorporated different clinical features and outcomes and have used different methodologies, and it is therefore difficult to draw meaningful conclusions from this body of evidence. Calls for collaborative trials [16-18] have led to little progress.

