### Assessing model performance

An important goal of a prediction model is to classify patients into risk groups. The developed model will produce a risk score for each individual that is based on the patient's own predictor values. We will then use a cutoff value to decide when a risk score is high (such that we predict an adverse outcome) and when it is low (such that we predict a good outcome); this will be our CDR. The calibration of the model will be assessed by classifying children into deciles ordered by predicted risk and considering the agreement between the mean predicted risk and the observed events in each decile. The derived CDR will be cross-validated by comparing the classification of each patient with his or her actual outcome, thus allowing an estimate of the sensitivity and specificity of the prediction model. Next, by varying the chosen cutoff level, we will be able to produce a receiver operating characteristic curve (ROC) summarising the sensitivity and specificity of the predictive rule across the range of cutoffs. The overall discriminatory ability will be summarised as the area under the ROC (AUC ROC) with the 95% confidence interval. The most suitable cutoff level can then also be detected.

Each predictive model will be tested by checking how it performs against the data from all but one of the studies in turn (cross-validation of intrinsic prognostic performance) [63] and by using the bootstrap procedure [64]. This will adjust for overoptimism in the estimation of model performance due to validation in the same data set that was used to develop the model itself.

The improvement in model performance by adding prognostic factors will be assessed by net reclassification improvement. By analysing the difference among the prognostic factors, a shrinkage factor will be calculated and the model will be corrected by this shrinkage factor. Note also that clustering of patients within studies will be accounted for in the model framework.

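### Net reclassification improvement, if computed at a low-risk cutoff well below the event rate, can credit an added predictor for moderate under-prediction of risk

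*Protocol article*

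**What the plan says.** Under Assessing model performance the article fixes the measure of added value: "The improvement in model performance by adding prognostic factors will be assessed by net reclassification improvement". It does not say whether the index is category-based or category-free, or which risk groups it uses.

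The same section describes a two-group decision rule: "We will then use a cutoff value to decide when a risk score is high". The level is left open, to be read from the ROC curve: "The most suitable cutoff level can then also be detected". No criterion for that choice is given.

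The purpose is stated elsewhere. The Background speaks of "A robust risk prediction model which identifies those children at very low risk of having a significant infection". The Discussion part of the Abstract wants to "define a group of individuals at low risk for febrile neutropenia who might be treated with reduced intensity or duration of antibiotic therapy" and also to "define a group of patients at very high risk of complications who could be subject to more intensive therapies".

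Other checks are planned. Under Model development, variables enter by an information criterion with P below 0.15, and those between 5% and 15% stay only if discrimination improves. Under Assessing model performance, calibration is examined by decile of predicted risk, AUC is reported with its confidence interval, and performance is tested by leaving out one study at a time and by bootstrap.

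**The concern.** On two groups, NRI adds the change in sensitivity to the change in specificity with equal weight. A rule that marks children for less treatment normally uses a cutoff well below the event rate, because a missed infection matters more than a false alarm. At such a cutoff, lowering everyone's predicted risk gains more specificity than it loses sensitivity. NRI can then rise although nothing has been learned and more children with events are labelled low risk.

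At stake is how extra tests are credited. The article says under Model development that costly tests must add considerable predictive power over simpler variables. If the expanded model under-predicts relative to the simpler one in a left-out study, the summed NRI could present that as a gain. Bootstrap and cross-validation correct optimism. They do not alter the weighting.

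**Working it through.** The article gives no cutoff, no event rate for the composite outcome, no AUC and no NRI value, so there is no figure of its own to reproduce.

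**Inputs (assumptions, shown as ranges)**
- Event rate e: 25% to 33%. The Abstract says three-fourths of patients do not need aggressive treatment. The Background says "There remain many episodes of febrile neutropenia (FNP), possibly two-thirds or more", in describing patients with no significant infection identified. Both are proxies for the composite outcome.
- Cutoff t: 5%, 10% and 13%. The last is the average risk in the low-risk group of one existing rule (Systematic reviews of existing knowledge), used only for illustration.
- Risk distribution: calibrated, normal on the logit scale, with SD 0.8, 1.0 or 1.4. For e = 25%, SD 1.0 gives AUC 0.74.

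**Weighting**
- Two-category NRI = ΔSe + ΔSp.
- Net benefit NB = e·Se − [t/(1−t)]·(1−e)·(1−Sp).
- Hence ΔNB/e = ΔSe + k·ΔSp, with k = [t/(1−t)]·[(1−e)/e].
- k = 1 only when t = e.
- For e = 25%, k = 0.158, 0.333 and 0.448 at t = 5%, 10% and 13%. For e = 33%, k = 0.107, 0.226 and 0.303.
- Relative to net benefit, NRI therefore overweights specificity about 2-fold (1/0.448) to 9-fold (1/0.107).

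**Under-prediction with no new information** (e = 25%, AUC 0.74, t = 10%, all logits lowered by 0.4)

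| | Calibrated | Under-predicting |
|---|---|---|
| Sensitivity | 0.951 | 0.890 |
| Specificity | 0.235 | 0.383 |
| Missed events per 1000 | 250 × 0.049 = 12.3 | 250 × 0.110 = 27.5 |
| Non-events labelled low risk per 1000 | 750 × 0.235 = 176.3 | 750 × 0.383 = 287.3 |
| Low-risk event rate | 12.3/188.6 = 6.5% | 27.5/314.8 = 8.7% |

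- NRI = −0.061 + 0.148 = +0.087.
- ΔNB = 0.25 × (−0.061) + (1/9) × 0.75 × 0.148 = −0.0153 + 0.0123 = −0.003.
- Over 36 settings (two event rates, three SDs, three cutoffs, shifts of 0.2 and 0.4 logits), NRI was positive in all (+0.005 to +0.087) and net benefit fell in all.

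**Limits of the effect** (e = 25%, AUC 0.74)
- The same 0.4 shift gives NRI −0.005 at t = 22% and −0.022 at t = 24%.
- With t = e, halving the predicted odds gives −0.083.
- At t = 10%, predicted odds × 0.5 give +0.139, × 0.33 give +0.169, × 0.2 give +0.121 and × 0.1 give −0.029. The reward is bounded and reverses.
- Category-free NRI under a uniform downward shift: all events move down (−1) and all non-events move down (+1), so the sum is 0.

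**Calibrated models as a control** (t = 10%)
- Nested models refitted by maximum likelihood at e = 25%: a useless predictor gives NRI 0.000. Useful ones give a positive NRI with a lower low-risk event rate (6.5% to 6.4%, 6.6% to 5.9%, 6.6% to 5.2%).
- A calibrated marker raising AUC from 0.69 to 0.74 gives NRI of about +0.09. Sensitivity falls by about 0.02, the low-risk event rate falls by about one percentage point, and net benefit rises by about 0.0045. NRI and net benefit agree in direction, but the sum does not show the loss of sensitivity.

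**The case against.** The strongest reply is that the article does not commit to the unfavourable case. NRI is never tied to the rule's cutoff. The intended very-high-risk group implies a second cutoff, and above the event rate under-prediction is penalised: at event rate 33%, AUC 0.80 and cutoff 40%, odds × 0.67 give NRI −0.051. A cutoff chosen to maximise sensitivity plus specificity would sit at the event rate for a calibrated model, where the effect vanishes. All this stands, and leaving the NRI details to a fuller plan is not itself a fault.

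A reader might infer that predictors are selected by NRI. The article does not support this: entry rests on the information criterion, P below 0.15 and discrimination. A uniform shift improves neither fit nor AUC.

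A reader might also infer that any cutoff below the event rate produces the effect, or that calibrated models would be credited unsafely. The calculations contradict both. The 36 settings cover only cutoffs up to 13% and shifts up to 0.4 logits.

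Decile calibration could reveal the problem: in the example, mean predicted risk is 19% against 25% observed. That also stands, but the article does not make the reading of NRI depend on calibration or say that calibration will be compared between the two models. AUC cannot detect the shift, because ranking is unchanged.

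**Conclusion.** The point holds conditionally. If NRI is computed on the two groups of the single-cutoff rule, and the cutoff lies well below the event rate, moderate under-prediction earns a positive NRI while the low-risk group becomes less safe and net benefit falls. The size is up to +0.087 over the assumed ranges (cutoff 5% to 13%, event rate 25% to 33%, shifts up to 0.4 logits). The worked example has 27.5 instead of 12.3 missed events per 1000.

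The exposure is mainly where the simpler and expanded models differ in calibration, which means left-out studies or after shrinkage. That is plausible with 23 data sets from 12 countries and with serum marker data that the article itself calls heterogeneous. It also assumes that NRI is evaluated there, which the article does not state. Between calibrated models NRI points the same way as net benefit, and the remaining weakness is that the sum can hide a fall in sensitivity. This is a worthwhile, cheap improvement to a stated measure. It does not show that the planned model would be unsafe.

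**What to change.** Replace the NRI sentence under Assessing model performance with wording such as: *The value of adding prognostic factors will be assessed by the change in net benefit at the low-risk cutoff the collaborative adopts, and over a range around it, using the same cutoff for both models. Changes in sensitivity, in specificity, and in the size and event rate of the low-risk group will be shown separately.*

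If NRI is kept, state its type and categories, report its event and non-event parts separately beside each model's calibration, and do not judge a predictor on the sum.

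The cost is a short change of wording and one further calculation from the same predictions, with no new data. The Discussion says no analyses have yet been undertaken, so the change can be made before results are seen. The downside is that reported gains for some markers will look smaller.

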### Validation in new data

We will compare the predicted and observed event rates to assess calibration (as described above) and the AUC ROC to assess discriminatory ability. If new data become available after the formation of the PICNICC Collaborative, they will provide an excellent test bed for the newly proposed model. Such an analysis is outside the initial scope of this project. We will update the model if it shows poor performance to adjust it to the new situation by recalibration or revision methods, depending on discrimination performance. Simple diagnostic test accuracy measures (such as positive and negative predictive values) will be computed for a hypothetical population (with its particular incidence rates) to aid clinical interpretation of the study results that define a low-risk group.

### Assessment of publication bias

We do not believe that publication bias will affect the data we obtain. We have sought to retrieve full data from the studies and so have sidestepped many of the problems of reporting bias. There may remain issues of different outcome collection and different outcome assessment methods, but these will not have been biased by collection and analysis of the predictive data. We have tried to avoid publication bias by making open calls for data which has been collected but not yet published, and we have probably secured three such data sets for analysis. This may be too few to undertake a formal assessment of the difference between the published and unpublished sources. We are also using the data for a purpose different from that used by the original data collectors. We are developing a prediction model, whereas the original researchers are interested only in the prognostic effect of particular variables. Furthermore, by obtaining the IPD, we have obtained outcomes and variables not reported by the original data collectors in any publication. However, to check whether our collection of studies may be affected by publication bias, we will display a funnel plot for each of the variables included in the final model to see whether there is asymmetry (that is, potential publication bias). We will use guidelines for assessing asymmetry recently published in *BMJ *[65].

### Publication policy

The main results of the meta-analysis will be published and presented under the PICNICC name, with PICNICC comprising groups supplying data for analysis as well as its advisory group. Any subsequent technical papers which describe innovations in the methodologies used in the meta-analysis will acknowledge the PICNICC Collaborative as the source of the data. The PICNICC Collaborative will disseminate the findings of its research widely at academic conferences and in journal publications, on the University of York website and in lay summaries of the research.

## Discussion

### Status of the project

Currently, the PICNICC Collaborative has completed study identification and invitation and has collected data derived from 23 data sets from 12 countries, including the Europe-wide European Organisation for Research and Treatment of Cancer studies. No data analyses have yet been undertaken. The opportunity to include data sets for the derivation of a new PICNICC CDR have now closed, but approaches may be made to the authors for consideration of inclusion of further data sets in subsequent validation testing or further refinements of the initiative.

### Further research opportunities arising from PICNICC

It is hoped that collaborations developed through the PICNICC project may also lead to a series of international studies to improve patients' experiences and outcomes with regard to infectious complications in cancer. One obvious follow-up study might be the use of the newly derived model in a RCT of alternative management approaches (for example, ambulatory oral antibiotics vs inpatient intravenous antibiotics). Other studies may include the investigation of genetic polymorphisms in determining the outcomes of infectious episodes; the prediction of specific infections which may require different management approaches, such as antibiotic-resistant bacteraemia; or the prediction of the risk of an episode of FNP.

The PICNICC Collaborative will provide data that will prove invaluable in the development of the methodology of IPD meta-analysis for risk prediction. This developmental work, which will be essential to developing the best possible model in PICNICC, is outside the core clinical questions set for the PICNICC Collaborative and will be undertaken as a series of linked projects. The problems to be addressed in developing the methodologies will depend on the nature of the data sets obtained. They may address issues regarding the analysis of missing data, the use of different imputation models, the modelling of multiple-episode data, the relative merits of prospective and retrospectively collected information, the use of alternative modelling techniques (such as CART, structured equation modelling, Bayesian techniques or neural networks), the comparison of episodic and patient-centred analyses and the use of categorical outcome variables. A short methodological protocol will be developed for each methodological investigation prior to commencement.

## Abbreviations

95% CI: 95% confidence interval; 95% CrI; 95% credible interval: CART: classification and regression tree; CDR: clinical decision rule; CRP: C-reactive protein; FNP: febrile neutropenia; IL: interleukin; IPD: individual participant data; RCT: randomised controlled trial.
